### Outcomes

2.8

The *primary outcome* of the study will consist in the impact of early mobilization after AMI on the ventricular remodeling in the post-infarction period, as assessed by CMR imaging.

*Secondary outcomes* of the study will be represented by rate of in-hospital mortality and the rate of repeated revascularization or MACE (including CV death or stroke) in patients with early mobilization as compared to those with delayed mobilization, and the effect of early mobilization on systemic inflammation in the immediate postinfarction phase.

### Participation timeline

2.9

Baseline (day 0):

Achieve written informed consent form all patients.Check all inclusion/exclusion criteria.Record demographic information, medical records, CV risk factorsPerform and record physical examination and 12-lead electrocardiography (ECG).Laboratory analysis (CBC, routine biochemistry, inflammatory biomarkers, acute adhesion molecules).Transthoracic echocardiography / speckle tracking.

Visit 1 (day 7 / discharge from the hospital):

hs-CRP assessment.

Visit 2 (month 1):

LGE-CMR (myocardial fibrosis/scar, infarct size, transmurality, remodeling).

Visit 3,4,5 (month 3,6,9)

Record results of physical exam, medical records, ECG.Transthoracic echocardiography / speckle tracking.

Final study visit (month 12)

Record results of physical exam, medical records, ECG.Transthoracic echocardiography / speckle tracking.End-point assessment.

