#### Transthoracic echocardiography

2.6.2

Transthoracic echocardiographic assessment will be performed at first visit in all patients, in the first days during the hospitalization for the acute coronary event. Speckle tracking technology will be used for evaluation of ventricular volumes and wall motion analysis, using a Vivid E9 ultrasound system (General Electric Vingmed Ultrasound, Horten, Norway).

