#### Late gadolinium-enhancement cardiac magnetic resonance (LGE-CMR)

2.6.3

All CMR images will be acquired with the use of a 1.5T Siemens Magnetom Aera equipment. The LGE-CMR will be used to quantify the infarct size, the extent of myocardial necrosis and the transmurality index, 10 minutes after gadolinium intravenous injection. Imaging data post-processing will be conducted with the use of Medis Q Mass 8.1 software (Medis, Leiden, the Netherlands), which involves manually tracing of the epicardial and endocardial borders, while setting the threshold for hyper-enhancement in the acquired image sequence.

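### The primary outcome is ventricular remodeling by CMR, but the schedule has a single CMR at month 1, so the named primary modality cannot measure change

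*Protocol article*

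**What the plan says.** Section 2.8 of the protocol article gives the primary outcome as the "impact of early mobilization after AMI on the ventricular remodeling in the post-infarction period, as assessed by CMR imaging". The primary objective in Section 1.2 matches it. Neither names a CMR parameter, a change score or a time point.

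Section 2.9 schedules imaging as follows:
- Day 0: echocardiography and no CMR ("Laboratory analysis (CBC, routine biochemistry, inflammatory biomarkers, acute adhesion molecules).Transthoracic echocardiography / speckle tracking").
- Visit 1, day 7 or discharge: only "hs-CRP assessment".
- Visit 2, month 1: "LGE-CMR (myocardial fibrosis/scar, infarct size, transmurality, remodeling".
- Visits 3 to 5, months 3, 6 and 9: echocardiography and no CMR.
- Final visit, month 12: "Transthoracic echocardiography / speckle tracking.End-point assessment", and no CMR.

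Section 2.6 lists CMR among the procedures without a visit. Section 2.6.3 says "The LGE-CMR will be used to quantify the infarct size, the extent of myocardial necrosis and the transmurality index" and also gives no visit.

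On echocardiography, Section 2.6.2 says that speckle tracking will assess ventricular volumes, and that "Transthoracic echocardiographic assessment will be performed at first visit in all patients, in the first days during the hospitalization".

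Sections 2.1 and 2.3 call the study non-randomised. Section 2.5 forms the groups by mobilization before or after 2 days from symptom onset. Section 2.7 runs the study from October 2019 to October 2020.

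**The concern.** The protocol describes remodeling as something that happens over time. Section 1.1 calls it dynamic and speaks of its regression, and Section 3.2 describes progression through LV dilatation and rising volumes. A single scan per patient shows the state of the ventricle on one day, not its course.

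In a randomised trial, a single post-treatment scan could still support a fair comparison between groups. Here the groups are formed by when patients were mobilized. Section 1.1 links guideline mobilization times to uncomplicated infarction, so patients mobilized late may plausibly have had worse infarcts. Section 3.2 names infarct size as one of the main determinants of remodeling. A month-1 difference in LV volume or scar could therefore reflect the initial infarct and LV size, the effect of mobilization, or both, and the named primary modality has no earlier measurement to help separate them.

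**Working it through.** **Step 1. Count the scans.** From Section 2.9, CMR scans per patient are 0 before month 1, 1 at month 1 and 0 afterwards. A within-patient change needs at least 2, so none can be computed from CMR.

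**Step 2. Place the scan relative to exposure.** Exposure is defined by a 2-day cut-off (Section 2.5). Month 1 falls after mobilization in both groups, so the scan cannot serve as a baseline.

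**Step 3. Find where change can be measured.** Echocardiography provides ventricular volumes (Section 2.6.2) at day 0 and months 3, 6, 9 and 12 (Section 2.9). Change from day 0 is available there, but in a modality that Section 2.8 does not name.

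**Step 4. Illustrate the size.** The protocol gives no power figure for the CMR outcome. The 90% power in Section 2.10 refers to major adverse cardiovascular events and does not bear on this point. The inputs are:
- From Section 2.10: 50 per group, two-sided alpha 0.05, 90% power. Using these for CMR is an assumption, as is the equal split, because no mechanism that would produce it is described.
- Assumed: correlation r between the baseline covariate and the month-1 CMR measure of 0.5 to 0.7.
- Assumed: baseline imbalance b of 0.3 to 0.5 SD.

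Detectable difference, unadjusted: (1.960 + 1.282) × √(2/50) = 3.242 × 0.2 = 0.65 SD.

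Detectable difference with baseline as covariate, 0.648 × √(1 − r²):
- r = 0.5: 0.648 × √0.75 = 0.56 SD
- r = 0.7: 0.648 × √0.51 = 0.46 SD

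False difference in an unadjusted comparison when mobilization has no effect, r × b, and the resulting rate of significant results at a nominal 5% (standard error 0.2 SD):
- r = 0.5, b = 0.3: 0.15 SD, about 12%
- r = 0.7, b = 0.3: 0.21 SD, about 18%
- r = 0.5, b = 0.5: 0.25 SD, about 24%
- r = 0.7, b = 0.5: 0.35 SD, about 42%

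The first pair of results concerns precision. The second set concerns validity, and matters more here.

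**Step 5. Check the follow-up visits against the study window.** October 2019 to October 2020 is about 12 months. If that window includes follow-up, a month-m visit falls inside it only for patients enrolled in the first 12 − m months: the first 9 months for the month-3 visit, 6 for month 6, 3 for month 9, and only the very start for month 12.

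**The case against.** A reader might infer that the plan cannot measure remodeling as a change at all. The documents do not support that: echocardiographic volumes are scheduled from day 0 to month 12. The defect is limited to the modality named in the primary outcome.

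A reader might also take the lack of a month-12 CMR as contradicting the end-point assessment at that visit. That does not follow either, since the assessment may refer to the clinical events in Section 2.8.

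The strongest defence is that Section 2.8 promises no change score, that Section 2.9 lists remodeling as a month-1 CMR reading, and that the article calls the study descriptive. Comparing LV state at month 1 is then a legitimate target. This stands in part: the comparison can be made, but it is confounded, and it is not the change or regression that the article speaks of.

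It is also fair to say that covariates usually belong in an analysis plan, which is not shown. The mismatch between primary outcome and visit schedule, however, lies in the protocol itself.

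On the baseline echo, doing it at the first visit is compatible with day 0. That it follows mobilization in the early group is possible under the looser wording in Section 2.6.2, but is not stated. This is a secondary ambiguity. It matters because this echo is the only LV baseline.

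Sections 2.2, 2.3 and 2.6.1 mention randomization, which would weaken the confounding argument. But the statements of design in Sections 2.1 and 2.3 say non-randomised, and no random allocation is described.

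**Conclusion.** The point holds in this form: CMR, the modality named for the primary outcome, is scheduled once, after exposure in both groups, and so cannot measure change. An unadjusted month-1 comparison cannot separate initial infarct and LV size from an effect of mobilization. This part rests on the documents alone.

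The size does not. A false difference of about 0.15 to 0.35 SD, against a detectable difference of about 0.65 SD unadjusted, depends on the assumed correlations, imbalance and group sizes. It shows that the bias could be material, not that it is present.

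The outcome and the schedule should be reconciled before analysis, because the primary conclusion depends on what the month-1 scan is taken to show.

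**What to change.** 1. Restate the CMR primary outcome in Sections 1.2 and 2.8 as a named month-1 LV measure, for example LV end-systolic or end-diastolic volume index. Describe it as LV state at month 1, not as change or regression of remodeling. Add the measure to Section 2.6.3, whose list of CMR quantities does not include volumes.
2. Analyse it with day-0 echo LV volume as a covariate. State that this baseline comes from a different modality, removes confounding only in part and does not measure initial infarct size.
3. Name the change in echo LV volume from day 0 as the measure of remodeling over time, at a follow-up visit that fits the study window. Reconcile Section 2.7 with the month-12 visit in Section 2.9, stating whether the dates cover enrolment only or follow-up too.
4. Align Section 2.6.2 with Section 2.9 so that the baseline echo is done at day 0 and before mobilization, and record the time of each.

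The cost is wording, one covariate and tighter timing of an echo already planned, with no extra scans. If the study window must be extended to reach the chosen echo visit, that is a further cost. The price in interpretation is a narrower CMR claim with residual confounding. If the sponsor wants change measured by CMR itself, earlier and later scans would have to be added.

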### Sample size

2.10

The study will enroll 100 patients with AMI who presented within the first 12 hours after the onset of symptoms and underwent successful revascularization of the culprit artery within the recommended timeframe, with TIMI 3 flow. Patients will be divided into 2 groups on the basis of the time interval from admission to mobilization: early (<2 days) mobilization group, versus delayed (>2 days) mobilization group. The sample size was calculated using Stat Mate 2.0 software, which indicated that a sample size of 50 subjects per group has a 90% power to detect an increase in major adverse CV events rates proportion of 3.28, with a significance level (alpha) of 0.05 (2-tailed).

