### Study design

2.1

This is a prospective, non-randomized, cohort study, carried out in a single-center, which aims to assess the link between early mobilization after AMI, systemic inflammation, and LV remodeling in patients with recent STEMI.

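### The only power statement is for MACE, a secondary outcome, with an effect size that cannot be interpreted as written; the CMR primary has none

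*Protocol article*

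**What the plan says.** The Sample size section (2.10) contains the article's only planning calculation. It names the software, a two-tailed alpha of 0.05, and the result that "50 subjects per group has a 90% power to detect an increase in major adverse CV events rates proportion of 3.28". The total of 100 is exactly twice 50.

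The Outcomes section (2.8) defines the primary outcome as the "impact of early mobilization after AMI on the ventricular remodeling in the post-infarction period, as assessed by CMR imaging", and the Study objectives section (1.2) makes the same choice. MACE appears among the secondary outcomes, as "the rate of repeated revascularization or MACE (including CV death or stroke) in patients with early mobilization" compared with delayed mobilization. No expected difference, standard deviation or precision is given for any CMR measure.

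On design, section 2.1 says "This is a prospective, non-randomized, cohort study". Sections 2.5 and 2.10 form the two groups by time to mobilization, with a cut at 2 days.

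**The concern.** There are two separate problems in one sentence.

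First, the endpoint. The sample size rests on a secondary outcome. A reader who sees 90% power will naturally attach it to the primary comparison, where it does not belong. If the CMR comparison shows no difference, that result could be weighed against a power figure that was never computed for it.

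Second, the effect size. A proportion, or an increase in a proportion, of 3.28 does not exist. The number must be on some other scale or carry a slip, and the sentence does not say which. It gives no MACE rate for either group and no time horizon, so the 90% cannot be checked even for the outcome it concerns.

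**Working it through.** **Inputs from the document.** n = 50 per group, two-sided alpha 0.05, claimed power 90%, effect 3.28 (all section 2.10). The reference MACE rate is not stated, so every rate below is an assumption.

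**Formula for two proportions** (normal approximation, pooled variance under the null, no continuity correction), with p̄ = (p₁ + p₂)/2:

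power = Φ{ [ |p₂ − p₁| − 1.96·√(2p̄(1−p̄)/n) ] / √( [p₁(1−p₁) + p₂(1−p₂)]/n ) }

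**Step 1: try to reproduce the 90%.** Taken literally, p₂ − p₁ = 3.28 or p₂ = 3.28 is outside the range 0 to 1, so no power exists. The stated figure cannot be reproduced without supplying both a scale and a reference rate.

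**Step 2: supply them in turn.** Worked example for a risk ratio of 3.28 at an assumed 5% reference rate: p₂ = 3.28 × 0.05 = 0.164, p̄ = 0.107, null SE = 0.0618, alternative SE = 0.0608. Then (0.114 − 1.96 × 0.0618)/0.0608 = −0.12, and Φ(−0.12) = 45%.

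| Reading of 3.28 | Assumed rates | Power, 50 per group |
|---|---|---|
| Risk ratio | 2% vs 6.6% | 20% |
| Risk ratio | 5% vs 16.4% | 45% |
| Risk ratio | 10% vs 32.8% | 80% |
| Risk ratio | 12.2% vs 40.2% | 90% |
| Risk ratio | 15% vs 49.2% | 97% |
| Odds ratio | any; best near 36% vs 64% | at most 83% |
| 3.28 percentage points | 1% vs 4.28% | 17% |
| 3.28 percentage points | 5% vs 8.28% | 10% |
| 3.28 percentage points | 20% vs 23.28% | 6% |
| 328% increase (ratio 4.28) | 8% vs 34.2% | 91% |
| Difference of 0.328 | 1% vs 33.8% | 99.6% |
| Difference of 0.328 | 33.6% vs 66.4% (least favourable) | 92% |

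Depending on the reading and the assumed rate, power runs from about 6% to nearly 100%. Some readings reach 90% and others cannot.

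**Step 3: what 50 per group offers the primary outcome.** No CMR difference or SD is given, so work in SD units for a continuous measure. The detectable difference at 90% power is (1.96 + 1.2816) × √(2/50) = 3.2416 × 0.2 = 0.648 SD by the normal approximation, or 0.655 SD with the t distribution: about 0.65 SD. Power for smaller differences, Φ(d/0.2 − 1.96):

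| True difference | Power |
|---|---|
| 0.5 SD | Φ(0.54) = 71% (70% by t-test) |
| 0.4 SD | Φ(0.04) = 52% (51% by t-test) |
| 0.3 SD | Φ(−0.46) = 32% |

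These assume 50 evaluable scans in each group. With an uneven split the same 0.65 SD carries less power. As an illustration only, an assumed 70/30 split gives about 84%.

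**The case against.** The strongest reply is that the 90% may well be right for MACE. If 3.28 is a decimal slip for 0.328, power is 92% or more at every reference rate tried. With a continuity correction, 50 per group is exactly what 20% versus 52.8% requires for 90% power. If 3.28 is a risk ratio, 12.2% versus 40.2% also gives 90%. The article condenses a fuller protocol, which may hold the rates. This stands: a reader might infer that the claim is false or that no reading rescues it, and the document does not support that.

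A reader might also call a 40% event rate implausible after successful revascularization. The document gives no expected rate. Its description of MACE lists CV death and stroke as components without saying they are the only ones, pairs MACE with repeated revascularization, and follows patients to month 12. Implausibility cannot be shown from these pages. Nor can it be said that the groups will be unequal. Section 2.10 plans 50 in each, and how that balance would be reached is simply not described.

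None of this touches the core. Condensation may explain a missing rate, but not a printed effect that is impossible as worded. Even a fully correct MACE calculation would not be a power statement for CMR remodeling.

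**Conclusion.** Wrong as written, in two respects. The stated 90% power belongs to a secondary outcome and does not apply to the primary one, for which no detectable difference is given. The MACE effect is impossible in its literal form and lacks a scale and a reference rate, so the 90% is uninterpretable rather than disproved.

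For the primary, 50 per group gives 90% power only for a difference of about 0.65 SD, and about 70% at 0.5 SD. This rests on a continuous CMR measure, a two-sided 0.05 test, an even split and no missing scans. The MACE range rests on assumed reference rates throughout.

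**What to change.** Keep N = 100 and rewrite section 2.10.

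- For the CMR remodeling parameter that the sponsor names as primary, state that 50 per group gives 90% power (two-sided alpha 0.05) for a difference of about 0.65 SD and about 70% power for 0.5 SD, before missing scans.
- Add that this assumes an even split, which grouping by mobilization time in a non-randomized cohort may not give.
- Delete the 90% MACE statement as the basis for N. Alternatively, restate it with both assumed event rates, the scale of the effect and the time horizon, and do not present it as the power of the primary comparison.

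The cost is wording only. The stated power becomes less favourable, and no extra patients are needed.

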## Discussions

3

This manuscript presents the protocol of a clinical descriptive, study, conducted in a single-center, with the purpose to analyze the impact of early mobilization in reducing LV remodeling, the complication rates and mortality in patients who had suffered a recent AMI. At the same time, the study aims to demonstrate the contribution of early mobilization to reduction of systemic inflammation, thus reducing the inflammation-mediated ventricular remodeling.

### Cardiac rehabilitation after AMI

3.1

After 50 years from the first implementation of a post AMI CR program, the clinical benefits and cost-effectiveness of CR are now unequivocally demonstrated by clinical evidence, CR becoming an indispensable component of patient-oriented care.^[28,29]^ Published results have documented that CR improves patient outcomes, on a magnitude similar to the reduction in mortality and morbidity rates obtained by aspirin therapy or percutaneous coronary intervention implementation, and probably with similar cost-to-benefit ratios.^[30]^

Supported by systematic reviews and meta-analyses documenting a reduced mortality,^[31]^ at this moment CR after AMI is a Class I recommendation from both European and American guidelines.^[28]^ Unfortunately, despite the body of professional recommendations indicating CR as the most important evidence-based intervention for secondary prevention after AMI, CR programs integration into daily practice proves to be a challenge. In despite of the availability of suitable CR programs, many studies demonstrate currently that only 25% of suitable patients are referred^[32]^ or finally take up any form of CR,^[33]^ with <10% participation in elderly subjects. Moreover, even when implemented, most of CR programs rely only on short-term strategies, with 30% to 40% of patients discontinued CR after first 6 months, and up to 50% dropping out after 1 year.^[34]^ A series of research indicates the barriers that hold responsibility for the underuse of CR are generally centered around patient, healthcare provider, health system and community levels.^[35]^ Patient involvement seems to be particularly challenging, therefore implementation of novel strategies is urgently needed to address this problem, as this approach can minimize the probability of subsequent coronary events while maximizing functional capacity.^[36]^ Home-based programs, community-based group strategies or internet-based programs may represent alternative approaches to structured supervised CR providing risk modification, education and guidance.^[37–40]^

### Ventricular remodeling after acute myocardial infarction

3.2

Progression of the LV remodeling leads to alterations in cardiac geometry, function and structure of the myocardium. This affects the ventricular contraction that becomes asymmetric. Therefore, LV dilates, the cardiac volumes increases and the stroke volume decreases.^[15,18,41,42]^

One of the most important determinants of the LV remodeling is the infarct size. However, in some situations, although the infarcted area has been enlarged, myocardial reparative response can prevent the development of LV remodeling.^[15,42,43]^ Studies proved that initiation of the LV remodeling process does not correlate only with the infarcted size. LV remodeling depends also on inflammatory response that involves local chemokine production, necrotic tissues removal and extracellular matrix formation.^[15,18,41–44]^ Several recent studies have proved that miRNAs play also an important role in LV remodeling. The reduced expression of miRNA after AMI correlates with a proliferation of cytokines to the fibroblast line, thus with cardiac fibrosis and consequently the reduction of myocardial vascularization favoring LV remodeling.^[45]^

### Impact of early mobilization on systemic inflammatory response after AMI

3.3

The inflammatory response after AMI plays an important role in cardiac repair especially in preventing the occurrence of adverse LV remodeling and the onset of heart failure.^[45–46]^ After AMI, the sudden death of cardiomyocytes occurs, leading to the emergence of a pro-inflammatory response necessary for the necrotic cell clearance cells from the infarcted area. Paradoxically, myocardial reperfusion therapy leads to the aggravation of this inflammatory process. Thus, overexpression of proteases – matrix metalloprotease MMP2 and MMP9 and an impairment of autophagosome clearance occurs, leading to activation of the RISK pathways. The most frequent outcomes are associated with cardiac dilatation, infarct area expansion and cardiac fibrosis.^[46–50]^

A large multiple cytoplasmic complex is formed that mediates activation of pro-inflammatory cells (IL-1, IL-6, IL-18, tumor necrosis factor) with critical role in amplifying the pro-inflammatory response. Thus, the activation of natural killer cells and inflammasomes represents the second stage of the cytokine response to AMI. Inflammasomes are cytoplasmatic complexes that typically contain one of the nod-like receptor family proteins capable to recognize and induce the inflammatory response after AMI.^[15,46,51]^ Endothelial cells are one of the major sources of pro-inflammatory chemokines responsible for molecular adhesion to the endothelial surface. With an important role in the recruitment of neutrophils, monocytes and lymphocytes in the infarcted area, endothelial cells increase reactive oxygen species production by activating various signaling pathways, which involve additional secretion of chemokines and cytokines.^[15,46,47]^

In the first minutes after AMI, blood cytokines invade the infarcted area through the CCL2 / C-C chemokine receptor type 2 signal pathway. Early reperfusion of the myocardial tissue reduces the number of cytokines accumulated in the infarcted area by stimulating the immune reaction and thus is necessary for a favorable cardiac response after AMI.^[52,53]^ On the other hand, an insufficient repair response may be responsible for cardiac rupture or LV aneurysm. In conclusion, mechanical properties of scar tissue are the determinants of AMI-related outcomes.^[54]^

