### Study population

2.3

The study will be a single-center, observational, non-randomized study including 100 patients with AMI, presenting with either STEMI or non ST-segment elevation AMI (NSTEMI).

Inclusion criteria:

Patients with AMI in the last 12 hours.Successful revascularization of the culprit artery within the first 12 hours after the onset of symptoms in STEMI or within first 48 hours in NSTEMI (according to the risk class).Signed written informed consent.

Exclusion criteria:

Patient refusal;Any condition that would contraindicate CMR examination;Women during pregnancy or lactation period;Women able to procreate without any contraceptive usage;Chronic kidney disease (glomerular filtration rate <60 ml/min/1.73m^2^) or acute renal injury that requires hemodialysis;Any type of neoplasia documented in the last 3 years before randomization;Expectation of life <1 year.

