### Study groups

2.5

This study will enroll 100 patients with AMI meeting the inclusion criteria, who will be distributed in two groups: group 1 – patients with early mobilization (<2 days after the onset of symptoms) and; group 2 – subjects with delayed mobilization after AMI (>2 days after the onset of symptoms).

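### Counting mobilization time from symptom onset (section 2.5) builds time to revascularization into the early/delayed label; the size is unknown and depends mainly on the NSTEMI share and on how many patients are mobilized near 48 h

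*Protocol article*

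**What the plan says.** The protocol article gives two starting points for the same 2-day cut. Section 2.5 (and the abstract) counts from symptoms: "group 1 – patients with early mobilization (<2 days after the onset of symptoms", with the delayed group beyond 2 days on the same clock. Section 2.10 counts from arrival: "Patients will be divided into 2 groups on the basis of the time interval from admission to mobilization". Neither counts from the revascularization procedure.

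Section 2.3 sets the permitted delay before that procedure: "Successful revascularization of the culprit artery within the first 12 hours after the onset of symptoms in STEMI or within first 48 hours in NSTEMI". It enrolls both infarct types, although section 2.1 describes the aim for STEMI only. Section 2.10 adds that patients "presented within the first 12 hours after the onset of symptoms".

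Sections 2.1 and 2.3 state that the study is not randomized. The primary outcome is remodeling on CMR, and systemic inflammation is among the secondary outcomes (sections 1.2 and 2.8). Section 3.3 says that "Early reperfusion of the myocardial tissue reduces the number of cytokines accumulated in the infarcted area" and calls this necessary for a favorable cardiac response. The same section also says that reperfusion therapy makes the inflammatory process worse.

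**The concern.** For anyone mobilized after the procedure, time from onset to mobilization is the sum of two intervals: onset to revascularization, and revascularization to mobilization. Only the second reflects mobilization practice. The first is a treatment delay that section 3.3 itself links to cardiac outcome.

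Cutting the sum at 48 h pushes later-revascularized patients toward the delayed group, even when staff mobilize everyone at a time after the procedure that has nothing to do with the earlier delay. This differs from clinicians holding back sicker patients, which is an additional problem. With no randomization, nothing in the design balances the delay. At stake is whether a remodeling difference on CMR can be read as an effect of mobilization.

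**Working it through.** The plan gives no figure for this point. Its sample-size calculation concerns MACE and plays no part here.

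**Inputs from the article.** Cut at 2 days = 48 h (2.5, 2.10). Revascularization up to 12 h in STEMI and 48 h in NSTEMI (2.3); the starting point of the 48 h is not repeated there, and I read it as onset. Presentation within 12 h of onset (2.10).

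**Step 1: onset clock.** Let R be onset-to-revascularization time and G revascularization-to-mobilization time. A patient is early if R + G < 48, that is, if G < 48 − R.

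| R | Window left for G | Share of 48 h used by R |
|---|---|---|
| 2 h | 46 h | 4% |
| 12 h (STEMI limit) | 36 h | 25% |
| 24 h | 24 h | 50% |
| 36 h | 12 h | 75% |
| 48 h (NSTEMI limit) | 0 h | 100% |

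Two STEMI patients both mobilized 38 h after the procedure, with R = 2 h and R = 11 h, score 40 h (early) and 49 h (delayed).

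**Step 2: admission clock.** The window is 48 h minus admission-to-revascularization time, taking admission to come first (inferred; the text does not say so). An NSTEMI patient who presents by 12 h and is revascularized at 48 h has waited at least 48 − 12 = 36 h in hospital, which leaves at most 48 − 36 = 12 h. For a STEMI patient with an assumed 0.5 to 2 h from admission to procedure, the window is 46 to 47.5 h, so it hardly varies.

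**Step 3: size in STEMI only (assumed distributions).** R uniform 1.5 to 12 h, so SD = 10.5/√12 = 3.03 h. G is lognormal and independent of R.
- Onset clock, median G 42 h, log-SD 0.25 / 0.35 / 0.50: the delayed group has longer R by 1.39 / 1.00 / 0.71 h, which is 0.46 / 0.33 / 0.23 SD. The chance of being labelled early is 56–62% if R < 4 h and 31–40% if R > 10 h. With a median of 36 h the gap runs from 0.24 to just under 0.5 SD.
- Onset clock, mobilization in two clusters (half around 24 h with SD 6 h, half around 72 h with SD 8 h): 0.01 SD. Few patients sit near the cut.
- Admission clock, 0.5 to 2 h from admission to procedure, independent prehospital delay of 0.5 to 10 h: about 0.01 SD.
- Procedure clock: 0.

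**Step 4: size with NSTEMI in the mix (assumed distributions).** R uniform 2 to 12 h in STEMI and 6 to 48 h in NSTEMI; admission 1 to 6 h after onset; G lognormal, log-SD 0.50, medians 24, 36 and 48 h, independent of R. Gap in mean R, delayed minus early, in SD:

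| NSTEMI share | Onset clock | Admission clock | Procedure clock |
|---|---|---|---|
| 0% | 0.23–0.25 | 0.18–0.22 | 0 |
| 30% | 0.68–1.33 | 0.69–1.40 | 0 |
| 50% | 0.86–1.35 | 0.86–1.38 | 0 (at most 0.01) |

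At 30% NSTEMI on the onset clock, mean R is 7.4–8.6 h in the early group and 15.3–24.1 h in the delayed group. Part of this gap is infarct type itself, because late-revascularized NSTEMI patients collect in the delayed group. The 0% row on the admission clock is larger than in step 3 because these assumptions allow in-hospital delays of several hours. The near-zero STEMI result therefore depends on that delay being short.

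**The case against.** The strongest counter-case has five parts.

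- **The admission clock is already in the plan and nearly cures the problem in STEMI.** This stands where admission-to-procedure delay is short. A reader might infer that both clocks fail alike within STEMI; the check does not support that. The admission clock fails mainly for NSTEMI revascularized late.
- **The size rests on assumptions.** This stands. The article gives no distribution of mobilization times, and section 1.1 cites guideline mobilization at 12 to 24 h. A median near the cut enlarges the STEMI gap, and two separate clusters remove it. A reader might go on to state an inflated false-positive rate. That needs a correlation between delay and outcome, which the documents do not give. With an assumed 0.3, the chance of a false result favoring early mobilization ranges from about 2.6% (two clusters) to 10% (median 42 h, narrow spread), against 2.5% without bias, so no single figure is defensible.
- **The direction for hs-CRP is not settled.** This stands. It is tempting to say that inflammation too is biased toward early mobilization. However, section 3.3 says both that early reperfusion lowers cytokine accumulation and that reperfusion therapy aggravates inflammation, and the first statement concerns the infarcted area rather than systemic hs-CRP at day 7.
- **Covariates may be in an analysis plan that is not shown.** This stands as to their absence, which is not counted here. The group rule is fixed in this article, and the point rests on that rule.
- **Onset is a legitimate anchor.** Section 2.6.1 times hs-CRP from the acute event, and the 12 h limit and the TIMI 3 requirement already narrow differences in reperfusion. This stands in part: in STEMI, R can use at most a quarter of the window. The onset clock can be kept, but the unadjusted comparison then does not isolate mobilization.

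**Conclusion.** The point holds for the onset clock of section 2.5. The label contains time to revascularization by arithmetic, and the design does nothing to balance it. Because section 3.3 ties early reperfusion to a favorable cardiac response, the primary remodeling comparison can show a difference with no mobilization effect. With NSTEMI included, the delayed group also gains NSTEMI patients, and the documents do not say how infarct type alone would move remodeling, so the net direction in the mixed population is not certain. For hs-CRP the direction is less certain still.

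The size is unknown. Under the assumptions above it is about 0 to 0.5 SD of time to revascularization in STEMI with a 36–42 h median to mobilization, and about 0.7 SD or more with 30% NSTEMI. The result assumes that mobilization follows the procedure, which the text does not require, and that post-procedure timing is independent of the earlier delay. It is worth correcting because sections 2.5 and 2.10 have to be reconciled in any case.

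**What to change.** When reconciling sections 2.5 and 2.10, classify patients for analysis by time from the end of revascularization to mobilization, and state how a patient mobilized before revascularization is classified. Alternatively, keep the onset or admission clock, name the one that applies, and adjust the remodeling and hs-CRP comparisons for onset-to-revascularization time and for STEMI versus NSTEMI.

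Either route is a sentence or two of text and uses times already needed to check eligibility and assign groups. Neither changes when anyone is mobilized. The costs: under the first route some patients near the cut change group and the group sizes shift; under either route confounding by clinical condition remains and has to be handled separately.
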